**4.3.3.1 - Work-up bias assessment**

Clinicians will assess the presence or absence of each study criterion for all blunt head injury victims presenting to the Ronald Reagan UCLA Medical Center, including a cohort of 368 patients who do not undergo tomographic imaging during their initial visit, but agree to participate in the long-term outcome evaluation. Research assistants will have the evaluating clinicians record their criteria assessments (onto paper forms – see Appendix B) as soon as they have obtained each patient’s informed consent. The research assistants will also record a coded study number along with each patient’s age, sex, race, and date of injury, as well as a preferred time and phone number for the follow-up survey. Patients who do not have phones will be given the option of returning to the emergency department for their survey, and the patient’s address will be recorded on the survey form in lieu of a phone number. A reminder to participate in the survey will be mailed one week prior to the survey date to each patient who elects to return to the emergency department for the follow-up survey.

The research assistants will maintain a calendar containing the call-back schedule for the follow-up survey. At the time of enrollment, the patient’s coded study number will be entered into the calendar on the date and time corresponding to the scheduled appointment for the long-term survey (i.e. three months after the patient’s visit). The exact scheduling of these appointments will be negotiated between the research assistant and the patient, with the proviso that the survey cannot take place prior to 90 days after the injury. The research assistants will be further encouraged to complete each survey within 100 days of the patient’s injury.

The research assistants will contact each patient at the time previously scheduled for their follow-up survey. If the patient is unavailable at the scheduled time, the assistants will attempt to re-contact the patient using the following schedule: two times on the day of the interview, once daily for five days after the date of the interview, and once weekly for three weeks after the date of the interview. Upon successful contact the assistants will either complete the survey or reschedule the interview depending on the patient’s preference. Contact will be abandoned, and the patient deleted from the work-up bias evaluation if the assistants are not able to contact the patient within four weeks of the scheduled survey date.

Once contact is established, the research assistants will administer the survey using the script presented in Appendix - D. Patients, or the care-takers of incapacitated patients, will be asked whether they sought care at another facility after their discharge, whether they received any x-rays or imaging studies, and if so, what type, and whether they received any treatments, hospital admission or brain surgery as a result of the injury. Patients will be considered to have had a significant intracranial injury if they had a neurosurgical procedure performed as a result of their injury. After the completion of each survey, the survey responses will be paired with matching criteria assessments to form a complete data record for each patient.

Criteria assessments, survey results and the contact information obtained on each follow-up patient will be retained in a secure, locked file that will be indexed using the coded study numbers. Data from this file will only be accessible to the research assistants and study administrators. Information from completed surveys and matching criteria assessments will be entered into a computer database for long-term storage, transmission and analysis. Data will be entered into the computer using a redundant input system where each data element is entered twice. This system will protect against keyboard and entry errors, and help ensure data integrity. The computer data will be indexed using the coded study numbers and will not contain information that could be used to identify individual patients. The final record for each patient will contain the patient’s age (if less than 90 years, or a 90+ designation for patients older than 90 years), sex, race, date of injury, presence or absence of each criterion, date of follow-up, whether the patient sought additional care, whether the patient received imaging (and if so, the type of imaging: skull films, CT, MRI), whether the patient received any treatment, whether the patient was admitted to the hospital for their brain injury, and whether the patient underwent a neurosurgical intervention (and if so, what type). All contact information and any linking patient identifiers will be destroyed once follow-up information has been obtained.

Research assistants will make weekly backup copies of the computerized database, at which time the data will be reviewed for exceptional events. Cases will be considered to represent false-negative events if the patient was classified as low risk by the decision instrument, yet required neurosurgery. Cases will be counted as true-positives if they required neurosurgery and were not classified as low risk by the decision instrument. The error in sensitivity produced by work-up bias will be determined by computing the difference between the true sensitivity, as measured among the entire cohort of head injured patients presenting to the UCLA site during the work-up bias assessment, and the sensitivity measured among patients from this site who were selected for imaging. The exact formula for this calculation is as follows:

[figure not shown]

Where:

TP_I_ = Number of imaged individuals requiring neurosurgery and labeled positive by the decision instrument (number of true-positives among imaged patients).

FN_I_ = Number of imaged individuals requiring neurosurgery and labeled negative by the decision instrument (number of false-negatives among imaged patients).

TP_W_ = Number of un-imaged individuals requiring neurosurgery and labeled positive by the decision instrument (number of true-positives among un-imaged patients).

FN_W_ = Number of un-imaged individuals requiring neurosurgery and labeled negative by the decision instrument (number of false-negatives among un-imaged).

Confidence limits for this measure will be calculated by applying boot-strap estimation to the entire UCLA cohort (both imaged and un-imaged patients) [73]. Estimates of the work-up bias associated with negative predictive value and specificity will similarly be calculated by computing the absolute difference of these values among imaged patients and the entire cohort.

These methods are similar to those used in assessing the potential for work-up bias in our previous derivation study (PHS Grant No. R01 HS08239). The methodology has shown to be reliable, and we were able to obtain follow-up survey information on 98% of the patients who agreed to participate in the study.

To verify the potential for work-up bias to with 1.0% requires a population of 368 head injury patients who do not receive CT imaging during their initial presentation. Thus we will enroll 368 consecutive patients in the work-up bias portion of the study.

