Injuries such as isolated linear or basilar skull fractures, solitary small cerebral contusions, localized subarachnoid hemorrhage less than 1 mm thick, thin subdural hematomas less than 4mm thick, isolated pneumocephaly, and closed depressed skull fractures that do not violate the inner table will not be considered to be significant injuries [63]. Coincidental or congenital abnormalities will also not be considered to be significant intracranial injuries. Chronic subdural hematomas, without evidence of acute change, will be considered to be coincidental injuries and will not be considered to be significant acute injuries. Chronic subdural hematomas that exhibit any recent change, or those that are of indeterminate age, will be considered to be acute significant injuries.

Research assistants, blind to classification by the decision rule, will review the medical records of patients with positive tomographic scans to determine whether or not the patient received neurosurgical intervention. The need for neurosurgical intervention is defined as any of the following within seven days of the initial injury [63]:

1 – Death due to intracranial injury.

2 – Intubation for management or support of head injury.

3 – Craniotomy, elevation of skull fracture or intracranial pressure monitoring.

Cases involving death or intubation will be reviewed by the physician liaison to determine, on the basis of their best clinical judgment, whether there was a causal relationship between the event and the patients intracranial injury. The liaisons will be instructed to consider these events as causally related to intracranial injury unless there is compelling evidence to the contrary. Patients will not be considered to have received neurosurgical intervention if their death is clearly due to causes unrelated to their head injury, or if they were intubated solely to expedite care.

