*Persistent vomiting* is evidenced by recurrent (more than one episode), projectile or forceful emesis (either observed or by history) after trauma.

*Coagulopathy* is any impairment of normal blood clotting such as occurs in hemophilia, secondary to medications (Coumadin, heparin, aspirin, etc.), hepatic insufficiency and other conditions.

*Age 65 years or more* is determined by available history.

**Appendix D – Scripted Survey Form for Long-Term Follow-Up of Patients Who Do Not Undergo Tomographic Imaging During Their Initial Evaluation**

*Script for contacting study participants by telephone for long-term follow-up.*

Hello, Mr/s.__________________, my name is __________________. I work with [name] at the UCLA Emergency Medicine Center, and we are working on a research study on head injury. Your participation is completely voluntary. If you don’t mind, I’d like to tell you a little more about the study, and what is involved in participation. Please know that it is your right to decline to participate in this study for any reason, at any time. In addition, whether your decision to participate or not will not affect any aspect of your future medical care.

The study is being done to make sure that patients who have been seen in the emergency room and who do not receive a type of x-ray called a head CT do not have any significant head injury. Your participation in this study would consist entirely of answering a few short questions, which will help us determine if you have had any problems that might have been caused by your head injury after you left the emergency room. We will not record your name or patient number, and your participation would be completely anonymous.

If you have any questions or concerns about your right as a research subject, you may contact the UCLA Office for Protection of Research Subjects. Their phone number is [contact], or you may write then at OPRS, [name].

Would you like to take part in the study?

Do you have any questions or concerns I can address for you about the study?

(If study participant answers affirmatively to participate, then present study related questions as follows:).

Did you return to the hospital or go to another facility after your discharge from the emergency room.

**🞎** Yes **🞎** No **🞎** Unknown

If yes, did you receive any x-rays or imaging studies?

**🞎** Yes **🞎** No **🞎** Unknown

If yes, do you know if you had the following types of x-rays taken?

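### The work-up bias assessment counts un-imaged patients by a different outcome and window from the primary one, so it does not measure the bias in the primary sensitivity and has no route to count a death

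*Protocol*

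**What the plan says.** Main study (Protocol 4.3.5.1.2): "The need for neurosurgical intervention is defined as any of the following within seven days of the initial injury". The list that follows has three entries: "Death due to intracranial injury", "Intubation for management or support of head injury", and craniotomy, fracture elevation or pressure monitoring. Section 4.3.7 makes sensitivity for this outcome primary.

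Un-imaged cohort (Protocol 4.3.3.1): 368 consecutive UCLA patients without a head CT are surveyed, and "the survey cannot take place prior to 90 days after the injury". The case rule is "Patients will be considered to have had a significant intracranial injury if they had a neurosurgical procedure performed as a result of their injury". A false negative is then a low-risk patient who required neurosurgery. For patients who cannot be reached: "Contact will be abandoned, and the patient deleted from the work-up bias evaluation if the assistants are not able to contact the patient", the limit being four weeks after the scheduled date.

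The Appendix D script opens its study questions with "Did you return to the hospital or go to another facility after your discharge from the emergency room". It goes on to imaging, any treatment, admission and brain surgery.

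Section 4.3.3.1 combines TP_I and FN_I (imaged) with TP_W and FN_W (un-imaged) to give the error in sensitivity, with bootstrap limits. All four counts are described only as patients requiring neurosurgery.

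**The concern.** The sub-study exists to find one kind of event: an instrument-negative patient who is not scanned and has a serious injury. The gravest form of that event is death, which is part of the primary outcome but not of the un-imaged case rule. If a relative reports a death, the script has no field for it and the rule does not count it. If nobody can be reached, the patient is removed.

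The windows differ too. An operation on day 30 makes an un-imaged patient a case, but an operation first performed on day 30 does not make an imaged patient one.

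At stake is the assurance drawn from this cohort. The expected number of events is near zero, so one event decides the result. If no un-imaged event is recorded, the two sensitivities are identical in the data and in every bootstrap resample containing an imaged case. The report would be zero bias with an interval of zero width, whether or not a low-risk patient had died.

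**Working it through.** **Definitions side by side**

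- Components: imaged patients have death, intubation or a procedure; un-imaged patients have a procedure only.
- Window: seven days from injury for imaged patients. For un-imaged patients it runs from injury to a survey at day 90 or later (day 100 encouraged, with up to four weeks of re-contact), with no seven-day cut.
- Source: records for imaged patients, with liaison review of deaths and intubations; a telephone script without those items or dates for un-imaged patients. Section 4.3.3.1 also requires the type of intervention in the final record, which the script never asks.
- Alternative reading: if *requiring neurosurgery* means procedures only in both groups, the components match, but the result is no longer the bias of the primary composite sensitivity. Either reading needs reconciling.

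**The plan's figure of 368**

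Inputs are α = 0.05 with α/2 in the tail, and X = N (section 3.2). The exact lower limit is then P_L = 0.025^(1/N).

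- N = 367: 0.989999
- N = 368: 0.990026

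So 368 reproduces as the smallest N with P_L of at least 0.99. Equivalently, 0 events in 368 gives an upper limit of 1 − 0.025^(1/368) = 0.997%.

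**Effect of deletion**

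Expected completion is 98% (section 4.3.9.1): 0.98 × 368 = 360.6, so about 361 complete and 7 are deleted. For x events in n, the exact upper limit is the 0.975 quantile of Beta(x + 1, n − x), which equals the protocol's F form.

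- 0/361 (the 7 deleted): 1.017%
- 1/368: 1.50%
- 2/368: 1.95%
- 7/368: 3.88%

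Losing 7 at random is trivial. Losing patients because they had the event is not.

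**Effect on sensitivity**

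The printed formula is not shown in the text at hand; from its description it is the difference between

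- TP_I / (TP_I + FN_I), and
- (TP_I + TP_W) / (TP_I + FN_I + TP_W + FN_W).

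The UCLA imaged case count is not given, so a range is assumed. The middle value is the average per site, 368 cases / 4 sites = 92. With FN_I = TP_W = 0 and one uncounted instrument-negative death (true FN_W = 1):

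- TP_I = 50: 50/51 = 98.0%, a drop of 2.0 points
- TP_I = 92: 92/93 = 98.9%, a drop of 1.1 points
- TP_I = 184: 184/185 = 99.5%, a drop of 0.5 points

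The drop is larger if the count is smaller. In each case the protocol's rule would report zero.

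**Direction**

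Omitted deaths and intubations in low-risk patients lower FN_W and pull the estimate toward zero. Operations after day 7 in low-risk patients raise FN_W and push it away from zero. The net sign is not fixed.

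**The case against.** The strongest reply is that deaths would come to light anyway. Section 4.3.9.1 allows contact with family, asks about diagnosis, hospitalization or intervention, and plans to screen revisits and neurosurgical admissions. An intubated patient's caretaker would probably report an admission. The database is reviewed weekly for exceptional events. The derivation study followed 1,266 un-imaged patients and reported no death or missed injury. The exact upper limit for 0/1,266 is 1 − 0.025^(1/1266) = 0.29%, so if lost patients resemble that cohort (an assumption), 7 of them carry at most about 7 × 0.0029 = 0.02 expected events.

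Much of this stands. Deaths are not always deleted, and the expected number is very small. What does not stand is that the safeguards close the gap. No rule turns a reported death into a case, and nothing passes the admission screen into FN_W or the deletion rule. The discharge review in 4.3.8.2 recognizes study patients from sheets printed with the CT request (4.3.4), which un-imaged patients do not have. A death at home or at another hospital is not captured.

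A reader might infer three stronger points that the documents do not support:

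- **The estimate is pulled toward zero.** It need not be, because late operations count only among un-imaged patients.
- **One lost death takes sensitivity to about 80% to 83%.** This needs one imaged UCLA patient per un-imaged patient: 368 × 1.2% to 1.4% = 4.4 to 5.2 cases, hence 4/5 to 5/6. No such ratio is given. The lost patient must also be instrument-negative; an instrument-positive death adds to TP_W and does not lower sensitivity.
- **A 2% loss breaks the 1.0% bound.** A missing fraction and a confidence limit are different quantities, and 1.017% against 1.0% is immaterial.

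It is also fair to say that a longer window can reveal late-presenting missed injuries, and that sensitivity analyses for non-contacts are often left to a SAP. The complaint is not that an analysis is absent, but that the protocol itself fixes deletion and a different case rule.

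**Conclusion.** The point holds: the work-up bias assessment, as written, does not estimate the bias in the primary composite sensitivity. The mismatch in components and window, the missing survey items and the deletion rule are all in the current text and do not depend on any assumption.

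The size does depend on assumptions. The loss of about 7 patients rests on the protocol's own 98%. The limits of 1.50% to 3.88% apply only if 1 to 7 of those patients had events, which the derivation experience makes unlikely. The 0.5 to 2.0 point drop in sensitivity assumes 50 to 184 imaged UCLA true positives, no other misses, and that the patient who died was instrument-negative.

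This should be fixed before follow-up starts, since unasked items are hard to recover later. It is not a flaw in the main result, because the primary sensitivity is computed in imaged patients and is unchanged.

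**What to change.** - In 4.3.3.1, define the un-imaged outcome for TP_W and FN_W by the composite in 4.3.5.1.2, and state that TP_I and FN_I use the same definition.
- Use the same seven-day window in the formula, and report events up to the 90-day survey separately, so that late-presenting injuries remain visible.
- Add items to Appendix D, answerable by family or a caretaker: death and its cause, intubation, type of procedure, and the date of each.
- Replace deletion of non-contacts. Check them against the revisit and neurosurgical-admission screen in 4.3.9.1 before identifiers are destroyed, then report the bias with the remainder counted once as non-events and once as misses.

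The cost is a few survey lines, a small IRB amendment and one bounding analysis. The reported bias range will be wider.

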**4.3.2.2 - Assessing the potential for work-up bias**

It is possible that a patient with a significant head injury could exhibit none of our study criteria *and* not be selected for tomographic scanning. Such a case would represent an undetected false-negative event; all combinations of our criteria would fail, and we would be unaware of the failure. Such cases would create work-up (verification) bias and lead to erroneous estimates of sensitivity and negative predictive value. It is not possible, within reasonable budget limitations, to track all blunt head injury victims for such an occurrence, however, it is possible to tract a screening subset to determine whether false negative events occur and to estimate the potential magnitude of work-up bias. Thus, the presence or absence of each screening criterion and long-term outcome will be determined on a cohort of 368 consecutive blunt head injury patients who present to the Ronald Reagan UCLA Medical Center, but do not undergo CT head imaging.

The clinician caring for these patients will invite them to participate in a long-term outcome study. Research assistants, present in the emergency department on a continuous basis, will contact interested patients (or their caretakers) during their initial visit and obtain informed consent to participate in a structured telephone survey to take place three months after the date of injury. Patients who agree to participate in the study will be asked to provide a preferred time and phone number for the follow-up survey. Patients who do not have phones will be given the option of returning to the emergency department for the survey. Additional details of the work-up bias assessment are included in later sections of this proposal.

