Informed consent will be obtained only on patients participating in the long-term follow-up survey at the Ronald Reagan UCLA Medical Center. Clinicians will assess the presence or absence of each study criterion for all blunt head injury victims presenting to this center. Cases selected for CT imaging will be entered into the study under the waiver of informed consent using the process described above. Patients who do not undergo tomographic imaging will be invited by their physicians to participate in the long-term outcome evaluation. Research assistants will provide information about the study and assist in obtaining informed consent from patients who express interest in participating in the study. Patients will not be enrolled in the follow-up study unless they (or their surrogates) provide informed consent.

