Errors in sensitivity and negative predictive value may also occur through biased enrollment. Practical concerns, such as cognitive impairment among head injury victims, make it impossible to obtain informed consent on all patients. To eliminate the potential for selection bias we instituted methodologies that allow us to conduct an observational study under a waiver of informed consent. This approach ensures that we will enroll all patients who undergo tomographic scanning (including those most likely to have intracranial injuries), but limits our ability to obtain CT scans on all blunt head injury victims. In this process, our methodology introduces the potential for workup bias. However, errors would occur only if a patient with a significant head injury exhibited none of our study criteria *and* was not selected for tomographic scanning. Such a case would represent an undetected false-negative event; the decision instrument would fail, and we would be unaware of the failure. Although such an event is theoretically possible, available studies indicate that essentially all significant head injury victims exhibit some symptomatology. As noted in our background discussion, there are no case reports describing significant intracranial injuries in an individual who does not exhibit at least one of our initial screening criteria. Furthermore, in our derivation study, we obtained follow-up evaluations on 1,266 patients who did not undergo computed tomography during their initial presentations. These evaluations revealed that a small minority of these patients ultimately received cranial imaging. However, none of these cases required hospitalization or neurosurgical intervention, and there were no cases of missed intracranial injuries or death among this cohort [65]. Thus, the potential for work-up bias is a theoretical possibility, but is of less practical concern. Furthermore, we will screen patient revisits and inpatient neurosurgical trauma admissions to identify patients who might produce such bias. Finally, as mentioned previously, we will obtain criteria evaluations and contact information for 368 consecutive blunt head trauma patients who present to the Ronald Reagan UCLA Medical Center and do not undergo emergent tomographic head imaging during their initial evaluation. We will contact these patients, or their family, three months after their enrollment to determine whether they were eventually diagnosed as having a significant intracranial injury or required hospitalization or neurosurgical intervention. The survey form used in these follow-up assessments is similar to the one used in the previous head injury study, and a copy of the survey form is presented in Appendix - D. Based on our previous experience, we estimate that we will be able to complete survey interviews on approximately 98% of the enrolled patients [65]. This process will effectively screen a large subset of patients who are not otherwise enrolled in the study, and will allow us to not only detect workup bias, but also estimate its magnitude. Thus, although we cannot completely eradicate the potential for measurement bias, our methodology makes it unlikely that it will be present without our knowledge.

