
**4.3.9.2 - Specificity**

Bias in the specificity measurements could result from misclassification of subjects, or from selection bias due to non-random exclusion of patients from the study. Such exclusions could produce a study population that does not represent trauma patients in general. If many patients omitted from the study have "no-risk" criteria then our measure of specificity will be too low; the converse is also possible. It is impossible to determine the direction of possible bias in our specificity measurements. Our specificity estimates, even if biased, would be very unlikely to change enough to substantially alter our conclusions. For example, if clinicians ordered tomography only for seriously injured patients, most of whom have at least one of the risk criteria, then the number of uninjured patients labeled negative by the criteria will be small and the specificity will be low. On the other hand, if clinicians order large numbers of tomograms on patients with no complaints, then the number of uninjured patients labeled negative by the criteria will be large and the specificity will be high. The first scenario would result in erroneously low estimates of cost savings using criteria, while the second scenario would over estimate savings, however, neither scenario would alter the number of patients who have injury and are identified as such by the criteria. Thus errors in specificity may affect cost-saving estimates but will have little influence on the validity of selective criteria. Furthermore, data collection at the Pittsburgh site will include imaged as well as un-imaged cases, and will provide a means of estimating the specificity of the instrument when applied to all blunt head injury patients.

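### The whole-cohort specificity in the work-up bias assessment pools all imaged UCLA patients with un-imaged patients who enter only by invitation and consent, so un-imaged patients are under-weighted

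*Protocol*

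**What the plan says.** The two groups at UCLA enter by different routes, both set out in Section 4.3.4. For imaged patients: "Cases selected for CT imaging will be entered into the study under the waiver of informed consent using the process described above". For the others: "Patients who do not undergo tomographic imaging will be invited by their physicians to participate in the long-term outcome evaluation", and then "Patients will not be enrolled in the follow-up study unless they (or their surrogates) provide informed consent". Section 4.3.2.2 adds a step of self-selection, since research assistants "will contact interested patients (or their caretakers) during their initial visit and obtain informed consent". Under Section 4.3.3.1 the criteria form for an un-imaged patient is filled in once consent has been given, and a patient who cannot be reached within four weeks of the survey date is removed from the evaluation.

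The same group is nevertheless described in Section 4.3.2.2 as "a cohort of 368 consecutive blunt head injury patients who present to the Ronald Reagan UCLA Medical Center, but do not undergo CT head imaging", and is called consecutive again in Sections 4.3.3.1 and 4.3.9.1.

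Section 4.3.3.1 defines the reference sensitivity "as measured among the entire cohort of head injured patients presenting to the UCLA site during the work-up bias assessment". It takes the bias in negative predictive value (NPV) and specificity as the absolute difference between imaged patients and that whole cohort, with confidence limits from a bootstrap of the pooled UCLA patients. It states no participation fraction and no weight.

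On un-imaged data for specificity, Section 4.3.9.2 says that "data collection at the Pittsburgh site will include imaged as well as un-imaged cases". Sections 4.3.2.2, 4.3.3.1, 4.3.4, 4.3.9.1 and Appendix E describe un-imaged collection only at UCLA.

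**The concern.** The accrual window runs until 368 un-imaged patients have consented, and every imaged patient in that window counts. If only a fraction of eligible un-imaged patients take part, they have too small a share of the pool. The imaged group was selected for suspicion of injury and probably has a lower share of patients free of all criteria, so the pooled specificity would be too low and the work-up bias in specificity would look smaller than it is. A bootstrap of the same pool cannot reveal this, because each resample keeps the same wrong proportions.

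The protocol recognises the hazard elsewhere. Section 4.3.9.1 says that practical concerns such as cognitive impairment "make it impossible to obtain informed consent on all patients", and gives this as the reason for the waiver. The group meant to measure selection effects is then enrolled by consent. At stake is the estimate of how the instrument's specificity differs between imaged patients and all blunt head injury patients at UCLA.

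**Working it through.** **The plan's own figure.** With X = N, the exact limit in Section 3.2 at α/2 = 0.025 gives N = ln(0.025)/ln(0.99) = 367.04, so 368. The 368 of Section 4.3.3.1 reproduces. It fixes how many un-imaged patients are followed and carries no information on what share of all un-imaged patients they are.

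**Inputs.**
- s_I = 13.7%, specificity in imaged patients, from the derivation study in Section 3.1 (outcome: clinically important injury).
- s_W, specificity in un-imaged patients: not in the protocol; assumed 60%.
- R, true ratio of un-imaged to imaged patients among the uninjured: not in the protocol; assumed 0.736 (736 per 1,000).
- c, fraction of un-imaged patients invited, consenting and reached: not in the protocol; varied. The 98% quoted in Sections 4.3.3.1 and 4.3.9.1 is completion among those who agreed or enrolled, so it does not supply c.

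**Formula.** Planned pooled specificity = (s_I + R·c·s_W)/(1 + R·c). The true value is the same expression with c = 1 and does not depend on participation.

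- True: (0.137 + 0.736 × 0.60)/1.736 = 0.5786/1.736 = 33.3%.
- c = 0.75: (0.137 + 0.552 × 0.60)/1.552 = 30.2%.
- c = 0.50: (0.137 + 0.368 × 0.60)/1.368 = 26.2%.
- c = 0.25: (0.137 + 0.184 × 0.60)/1.184 = 20.9%.

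The work-up bias in specificity (whole cohort minus imaged) is truly 33.3 − 13.7 = 19.6 points. The plan would report 16.5, 12.5 and 7.2 points.

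**Range.** For R from 0.5 to 2 and s_W from 30% to 70%, the shortfall at c = 0.6 is 1.7 to 7.0 points.

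**Participation related to instrument status.** With R = 1 and s_W = 50%, true specificity is 31.8%. If low-risk patients participate at 40% and the others at 80%, the pool gives 21.0%; with the rates exchanged it gives 33.5%. The error can then go either way.

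**NPV.** For clinically important injury, imaged NPV in the derivation study is 1,752/1,768 = 99.1%. With no misses among un-imaged patients, R = 1 and s_W = 50%, pooled NPV is 99.81% at c = 1 and 99.65% at c = 0.4. Over the grid of R and s_W above, the change from c = 1 to c = 0.4 is about 0.1 to 0.2 points. For neurosurgery, none of the 16 derivation misses needed intervention (Section 2). If that recurs and no un-imaged patient is missed, NPV is 100% at every c.

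**Sensitivity difference.** If no un-imaged patient needs neurosurgery, TP_W = FN_W = 0, the two sensitivities are equal and the difference is zero whatever the weights.

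**The case against.** The protocol is open about consent: Section 4.3.3.1 describes the 368 as patients who agree to take part. Sections 4.3.3.1 and 4.3.4 say clinicians assess criteria in all UCLA head injury patients, and Appendix E asks the research assistants to seek consent from all of them and to check that all are enrolled and surveyed. Surrogate consent partly answers the cognitive-impairment problem. These aims reduce non-participation but cannot override a consent requirement, and the form for an un-imaged patient follows consent. It may also be said that adjustment for non-participation belongs in a statistical analysis plan. Here, however, the protocol itself fixes the cohort, the formula and the bootstrap population.

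Three stronger inferences do not stand. A reader might infer that NPV and the primary sensitivity result are also materially wrong; the working shows NPV barely moves and the sensitivity difference moves only if an un-imaged neurosurgical case occurs. A reader might infer that the projected savings rest on this pool. They do not: Section 1 counts scans in no-risk patients, that is, among imaged patients, and Section 2 uses the derivation study's 12.9%. Finally, a reader might infer that Section 4.3.9.2 moves the 368-patient cohort to Pittsburgh and should simply say UCLA. That section does not name the cohort and the site list is not shown, so which text is right cannot be decided from the protocol.

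**Conclusion.** The point holds for specificity. As written, the whole-cohort estimator mixes complete capture of imaged patients with partial capture of un-imaged patients and treats the result as everyone who presented. Its specificity, and the work-up bias derived from it, are wrong unless capture is complete or specificity is the same in both groups. If un-imaged specificity is the higher and participation is unrelated to instrument status, the error is toward the imaged value: about 3 points at 75% participation, 7 at 50% and 12 at 25% in the illustration. Those sizes rest on assumed un-imaged specificity, ratio and participation; only the 13.7% comes from the protocol, and it refers to clinically important injury, whereas the follow-up outcome in un-imaged patients is neurosurgery. The effect is confined to a supporting estimate and does not touch the primary outcome. The Pittsburgh and UCLA statements are a separate inconsistency to be reconciled.

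**What to change.** 1. During accrual, have the UCLA research assistants, who are already in the department continuously, keep an anonymous count of all un-imaged blunt head injury patients: invited, consented and completed, with age group and criteria status where the IRB permits.
2. In Section 4.3.3.1, give imaged patients weight 1 and each followed un-imaged patient the inverse of the captured fraction, by stratum where logged. Use these weights in the whole-cohort specificity, NPV and sensitivity and in every bootstrap resample. In the illustration at 50% participation, weight 2 turns 368 into 736 and restores 33.3%.
3. State the assumption that participation is unrelated to instrument status within strata, and give a sensitivity range for when it is not; one overall weight does not repair differential refusal.
4. Change the description to consecutive consenting patients in Sections 4.3.2.2, 4.3.3.1 and 4.3.9.1, and report participation.
5. Reconcile Section 4.3.9.2 with Sections 4.3.2.2, 4.3.3.1, 4.3.4, 4.3.9.1 and Appendix E on where un-imaged patients are studied.

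The cost is a small logging task that must fit the IRB terms, and wider intervals for the weighted estimates. The count has to be made during accrual, because the denominator may not be recoverable later.
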